### Inclusion criteria

2.5

Age 18–75 years.Patients with breast cancer or malignant lymphoma who develop frequent PVCs after receiving anthracycline therapy: those with more than 500 PVCs per 24 h or those with paired or consecutive PVCs.TCM diagnosis of QYD syndrome.Voluntary signing of informed consent.

### Exclusion criteria

2.6

Severe coronary artery disease or heart valve disease that is difficult to control with medication, or associated with hemodynamic instability.Pacemaker or implantable cardioverter defibrillator (ICD) implantation.Severe complications related to the primary cancer, potentially life-threatening.History of bleeding within the past month, including cerebrovascular, gastrointestinal, respiratory, urinary tract, or other organ bleeding.Severe psychiatric disorders.Allergy to any components of the study drug.Unexplained persistent elevation of transaminases (greater than three times the upper limit of normal).Severe renal dysfunction: estimated glomerular filtration rate (eGFR) < 45 mL/(min·1.73 m^2^).Severe infection.Pregnancy or breastfeeding.Concurrent oral cyclosporine use.Life expectancy of less than 2 years.Participation in other clinical trials within the past month.

### Termination criteria

2.7

The treatment should be considered for discontinuation under the following conditions:
The participant has the right to discontinue treatment at any time and for any reason.An allergic reaction clearly related to the study drug occurs.Adverse symptoms, signs, or abnormal test results clearly related to the study drug occur.The investigator determines that discontinuation of the study is necessary.Pregnancy occurs during the study in a female participant.Throughout the trial, efforts should be made to ensure that participants receive the standard dose of the study drug for the long term. Patients who discontinue the study drug should resume treatment as soon as possible after ruling out the aforementioned conditions and continue follow-up as scheduled.

### Withdrawal criteria

2.8

All eligible participants have the right to withdraw from the study at any time and for any reason. However, unnecessary withdrawals should be minimized. When a participant decides to withdraw, we will contact the patient or their relatives via telephone or in-person visits to confirm the reason for withdrawal whenever possible. Upon withdrawal, the remaining study drug will be collected, and a final assessment will be conducted. Efforts will be made to complete the case report form (CRF), document the reason for withdrawal, and follow up on endpoint events in withdrawn patients. If the withdrawal is due to an adverse event, it must be recorded in the CRF.

### Screening and recruitment of participants

2.9

We will conduct regular evaluations of breast cancer and malignant lymphoma patients undergoing anthracycline-containing chemotherapy regimens in the outpatient and inpatient departments of three hospitals. We will implement the following screening workflow to maximize identification of eligible participants. (1) Pre-chemotherapy: 24 h Holter will be performed before the first chemotherapy cycle, together with medical history review, to rule out pre-existing frequent PVCs. (2) During chemotherapy: 12-lead ECG will be obtained at each cycle. Additionally, 24 h Holter will be repeated every four cycles, and whenever clinically indicated (triggered by abnormal ECG or symptoms). (3) Post-chemotherapy follow-up: 12-lead ECG will be performed at each scheduled follow-up visit, and 24 h Holter will be repeated if clinically indicated (abnormal ECG or symptoms).

Based on the inclusion and exclusion criteria, eligible participants will be recruited. Each patient will receive either a printed or electronic version of the recruitment advertisement. The advertisement will provide a brief description of the study objectives, procedures, potential benefits, and risks. Each eligible participant will sign a consent form provided by study personnel prior to enrollment. Participants will not be involved in the design, conduct, and reporting of the trial.

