**Methods:**

This multicenter, randomized, double-blind, placebo-controlled trial will assess the efficacy and safety of SMY in treating frequent PVCs induced by anthracycline chemotherapy. A total of 212 patients with breast cancer or malignant lymphoma undergoing anthracycline-based chemotherapy, who have been diagnosed with new-onset frequent PVCs and *Qi* and *Yin* deficiency syndrome, will be enrolled. Participants will be randomly assigned to receive either SMY or a placebo for 8 weeks, alongside standard medications. The primary outcome is the reduction rate in PVC frequency. Secondary outcomes include PVC symptom scores, Traditional Chinese Medicine syndrome scores, cardiac dysfunction biomarkers, and major adverse cardiovascular events.

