## Introduction

1

Since the 1990s, advancements in cancer diagnosis and treatment have significantly prolonged the survival of cancer patients, making cardiovascular disease (CVD) the leading cause of mortality (1, 2). Consequently, increasing attention has been directed toward the cardiovascular adverse effects associated with cancer therapies. Anthracyclines, a key component of many first-line chemotherapy regimens, exhibit a well-documented dose-dependent risk of anthracycline-induced cardiotoxicity (ACT) (3, 4). ACT often manifests as cardiac dysfunction (3%–48%) and arrhythmias (10%–65.5%), posing a significant threat to patients' quality of life and prognosis (5–7). Premature ventricular contractions (PVCs) are common in the general population (8, 9). Asymptomatic or mildly symptomatic PVCs with low burden and preserved ventricular function are generally considered benign. However, frequent PVCs have been associated with an increased risk of heart failure and mortality (10). Among anthracycline-induced arrhythmias, PVCs are one of the most common types, with a tendency for increased PVC burden following chemotherapy (11–14).

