### Study overview

2.1

This trial is a multicenter, randomized, double-blind, placebo-controlled clinical study designed to evaluate the efficacy and safety of SMY in treating frequent PVCs associated with QYD syndrome induced by anthracycline chemotherapy. We will screen participants among breast cancer and malignant lymphoma patients undergoing chemotherapy with anthracycline-based regimens. Eligible participants will be enrolled in the trial after providing written informed consent and will be randomly assigned in a 1:1 ratio to either the intervention group or the placebo control group. A total of 212 participants will be recruited for this trial, with both the treatment and follow-up periods lasting 8 weeks. The study design is illustrated in Figure 1.

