### Randomization and blinding

2.11

Participants will be randomly assigned to either the intervention group (SMY group) or the placebo control group in a 1:1 ratio using a centralized web-based randomization system. Randomization will be stratified by study center, and the sequence will be computer-generated with permuted blocks of variable sizes within each center to ensure balanced allocation while minimizing predictability. The allocation sequence will remain concealed from participants and study personnel, including physicians, investigators, data collectors, and statisticians, to prevent selection bias.

This trial will be conducted in a double-blind manner, ensuring that both participants and study personnel remain unaware of treatment assignments throughout the trial. To ensure effective blinding, SMY and its placebo will be designed to be indistinguishable in appearance, smell, taste, and packaging.

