#### Standardized western medicine treatment

2.13.3

All participants will receive standardized Western medicine treatment individualized to clinical conditions, including:
Physician-determined chemotherapy regimens incorporating anthracyclines (21, 22).Primary prevention of ACT, recommended by clinical guidelines (26), may include dexrazoxane, angiotensin-converting enzyme inhibitors (ACEIs) or angiotensin II receptor blockers (ARBs), β-blockers, and/or statins, tailored to individual patient risk profiles.Guideline-directed therapy for PVCs (23). For most symptomatic patients, β-blockers are the first-line treatment. Other standard options, including antiarrhythmic drugs (AADs) and catheter ablation in selected cases, are permitted as clinically indicated.Medications for hypertension, diabetes, dyslipidemia, and other comorbidities, as clinically indicated.

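### Enrolled patients are described as undergoing anthracycline chemotherapy, but eligibility also admits patients who have finished it, and chemotherapy phase at entry is not a planned baseline item, covariate or subgroup

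*Protocol article*

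**What the plan says.** All references are to the protocol article.

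**Statements that point to patients on chemotherapy**
- Abstract, Methods: "A total of 212 patients with breast cancer or malignant lymphoma undergoing anthracycline-based chemotherapy, who have been diagnosed with new-onset frequent PVCs". This describes the patients to be enrolled.
- 2.1 Study overview: "We will screen participants among breast cancer and malignant lymphoma patients undergoing chemotherapy with anthracycline-based regimens".
- 2.13.3 Standardized western medicine treatment: "All participants will receive standardized Western medicine treatment individualized to clinical conditions, including", and the first item listed is "Physician-determined chemotherapy regimens incorporating anthracyclines".

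**Statements that also admit patients who have finished**
- 2.5 Inclusion criteria: "Patients with breast cancer or malignant lymphoma who develop frequent PVCs after receiving anthracycline therapy". It sets no upper limit on time since the last dose, and neither do the exclusion criteria in 2.6.
- 2.9 Screening, step (3): "Post-chemotherapy follow-up: 12-lead ECG will be performed at each scheduled follow-up visit, and 24 h Holter will be repeated if clinically indicated".

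**What the analysis takes into account**
- 2.11: "Randomization will be stratified by study center". No other stratification factor is named.
- 2.17: the primary linear model has treatment group, centre and baseline 24 h PVC count. The fully adjusted model adds a list that includes cumulative anthracycline dose but not phase or time since last dose. The subgroups are those covariates plus quartiles of baseline PVC burden.
- 2.14.4: the baseline oncology data include regimen and cumulative dose. They do not include whether anthracycline treatment is ongoing or the date of the last dose.

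**The concern.** The primary outcome (2.14.1) is the percentage reduction in 24 h PVC count between baseline and week 8. A participant in mid-course may receive further anthracycline during those 8 weeks, and a participant found in post-chemotherapy follow-up will not. The Introduction calls the cardiotoxicity risk of anthracyclines dose-dependent. It is therefore reasonable to suspect that PVC counts, and possibly the effect of the study drug, behave differently while the presumed cause continues and after it has stopped.

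If both kinds of patient are enrolled, the estimate averages over them in proportions that recruitment happens to produce, and the abstract's description of the population does not fit the result. With phase absent from the stated analysis, there would be no pre-specified way to show whether the two groups responded alike. A variable that may explain part of the outcome variance would also stay in the error term.

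**Working it through.** **1. Do the passages agree?** For a patient who completed anthracycline chemotherapy some time ago and is then found to have frequent PVCs:

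| Place | Is this patient covered? |
|---|---|
| Abstract, Methods | No: enrolled patients are undergoing chemotherapy |
| 2.1 | Not if read as status at entry; yes if read as the cohort under surveillance |
| 2.5 and 2.6 | Yes, at any interval since the last dose |
| 2.9, step (3) | Yes: this is how the patient is found |
| 2.13.3 | The first listed item does not apply; the lead-in allows individual tailoring |

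The abstract conflicts with 2.5 and 2.9. Sections 2.1 and 2.13.3 are ambiguous.

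**2. The plan's own sample size (2.10).** Inputs: difference 60 − 35 = 25 points, SDs 39 and 55, two-sided 5%, power 95%, 10% loss.
- Pooled SD = √((39² + 55²)/2) = √2273 = 47.7.
- n per group = 2 × (47.7 × (1.960 + 1.645)/25)² = 94.5, rounded up to 95. Then 95/0.9 = 105.6, so 106 per group and 212 in total.

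The stated figures reproduce. Power at 95 per group is 0.951 by the normal approximation and 0.949 by the Welch t test.

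**3. A mean shift between phases, left out of the model.** The documents give neither the share p of post-chemotherapy patients nor the difference D in mean percentage reduction between phases. Both are assumed here. Adding the phase variance on top of the planning SDs gives SD = √(2273 + p(1 − p)D²).

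| p | D | Added variance | Power at 95 per group | n per group for 95% power |
|---|---|---|---|---|
| 0.2 | 20 | 64 | 0.946 | 98 |
| 0.5 | 20 | 100 | 0.943 | 99 |
| 0.2 | 40 | 256 | 0.929 | 106 |
| 0.5 | 40 | 400 | 0.915 | 112 |

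If the planning SDs already contain the phase variance, no planned power is lost. Phase would then account for 100/2273 = 4.4% (D = 20) or 400/2273 = 17.6% (D = 40) of outcome variance at p = 0.5, which adjustment could recover as precision.

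**4. Chance imbalance.** With 106 per group and p = 0.5, the 95% range for the difference in phase share between arms is ±1.96 × √(2 × 0.25/106) = ±13.5 percentage points. Multiplied by D, this shifts the unadjusted difference by up to 2.7 points (D = 20) or 5.4 points (D = 40). The 95% half-width of the treatment difference itself is 1.96 × 47.7 × √(2/106) = 12.8 points.

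**5. A treatment effect that differs by phase.** The pooled effect is (1 − p) × 25 + p × e, where e is the assumed effect after chemotherapy and the SD is 47.7.

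| e | p = 0.2: effect, power | p = 0.5: effect, power |
|---|---|---|
| 12.5 (half) | 22.5, 0.90 | 18.75, 0.77 |
| 0 | 20.0, 0.82 | 12.5, 0.44 |

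Nothing in the documents indicates such an interaction. The table shows only where a larger loss could arise.

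**The case against.** The strongest defence is that this is mostly loose wording.

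- **Source cohort.** Sections 2.1 and 2.9 can be read as describing the cohort placed under surveillance, which is then followed before, during and after chemotherapy. On that reading step (3) is consistent with 2.5. Patients found through the workflow would also have had a Holter before their first cycle, so they need not be long-term survivors. This stands for 2.1 and 2.9, but not for the abstract, which applies the word to those enrolled.
- **Background treatment.** A reader might infer from 2.13.3 that every participant must receive anthracycline, so that a patient who has finished could not follow the protocol. The text does not support this. The treatment is individualised, and other items in the same list are optional or apply only to selected patients.
- **Prognostic evidence.** A reader might take phase to be a known prognostic factor. The documents do not show that. The Introduction reports PVCs "with a tendency for increased PVC burden following chemotherapy", which does not separate patients on treatment from those who have finished. The dose-dependence it cites concerns the risk of cardiotoxicity, not the 8-week course of established PVCs. The different course remains an inference.
- **Partial handling.** Cumulative dose is a pre-specified covariate and subgroup, and regimen is recorded. This helps, but the same cumulative dose can belong to a patient in mid-course or one who has finished. It also enters only the fully adjusted model and the subgroups.
- **Condensed article.** The date of last dose is a case-report-form detail that an article may omit. That is fair, so its absence alone would be no finding. The point rests on statements in the article that disagree and on the analysis factors it lists.
- **Remedy.** A mixed eligible population is a legitimate target, and the choice of covariates is a judgement. A two-level phase variable is also crude, because an ongoing patient may receive the last cycle soon after randomisation. Both remarks stand and limit the weight of the point.

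**Conclusion.** The point holds as an inconsistency in the target population, together with a plausible baseline factor that the stated analysis does not use. The abstract describes patients on chemotherapy, while 2.5 and 2.9 admit patients who have finished, at any interval. Phase is absent from the strata, baseline items, covariates and subgroups.

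A reader might infer that the treatment comparison is biased, or that the 2.7 or 5.4 points in step 4 are an error in the result. They are not. Randomisation protects the comparison, and those shifts are chance variation already inside the standard error.

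The consequences are interpretability and some precision. Under assumed shares of 20% to 50% and phase differences of 20 to 40 points, a pure mean shift leaves power between 0.946 and 0.915, against about 0.95 planned. Larger losses need a treatment-by-phase interaction, for which the documents give no evidence. The sample-size arithmetic is correct. The change is worth making because it is cheap, not because the trial is at serious risk without it.

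**What to change.** 1. Reconcile the abstract, 2.1, 2.5, 2.9 and 2.13.3 on whether patients who have finished chemotherapy belong to the population and, if so, whether time since the last dose is limited. Which answer is right is for the trial team to decide.
2. If both phases stay, add to 2.14.4 whether anthracycline treatment is ongoing or completed at randomisation, and the date of the last anthracycline dose. Define ongoing from what is known at randomisation, so that it remains a baseline variable.
3. Add phase to the pre-specified covariates of the fully adjusted model in 2.17 and, optionally, to the primary linear model.
4. List phase as a pre-specified subgroup with the interaction test already planned for the others.
5. Fix all of this before unblinding, so that it counts as pre-specified.

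The cost is revised wording, a small addition to the baseline form that should be obtainable from treatment records, and one model degree of freedom. No extra visit or patient is needed. The drawback is one more subgroup in a list for which 2.17 plans no multiplicity adjustment, so its result should be read as descriptive.

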### Sample size

2.10

A previous RCT demonstrated that after 4 weeks of treatment, the number of PVCs within 24 h decreased from 15,138 ± 7,597 to 5,686 ± 5,940 in the intervention group. While in the placebo group, the number decreased from 14,529 ± 5,929 to 10,592 ± 8,009 (25). The reduction in PVC counts for both groups was converted into reduction rates, which were 62.44% ± 39.24% in the intervention group and 27.10% ± 55.12% in the placebo group. The standard deviation (SD) of the reduction rate was estimated by dividing the reported post-treatment SD of PVC counts by the baseline mean number of PVCs.

Based on these findings, we assumed that the mean percentage reduction in 24 h PVC counts would be 60% in the intervention group and 35% in the placebo group, with SDs of 39% and 55%, respectively. To detect a between-group difference of 25% in the percentage reduction rate with 95% power at a two-sided significance level of 5%, a total of 95 participants per group would be required. Allowing for a 10% loss to follow-up, the final required sample size was set at 212 participants, with 106 participants allocated to each group.

Each participating center has a high volume of patients. Adequate study personnel will be assigned to screen, monitor, and recruit potential participants to ensure that the target sample size is achieved.

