#### Primary outcome

2.14.1

Percentage reduction in anthracycline-induced frequent PVCs, which is calculated by subtracting the post-treatment 24 h PVC count at 8 weeks from the baseline 24 h PVC count, then dividing the result by the baseline 24 h PVC count, and multiplying by 100%.

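### The 39% and 55% SDs behind the sample size are not SDs of the per-patient percentage reduction, so the stated 95% power is unsupported in either direction

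*Protocol article*

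**What the plan says.** Section 2.10 starts from an earlier randomized trial measured after 4 weeks of treatment. In its active arm the 24 h count "decreased from 15,138 ± 7,597 to 5,686 ± 5,940 in the intervention group". In its placebo arm "the number decreased from 14,529 ± 5,929 to 10,592 ± 8,009". The protocol turns these into reductions of 62.44% ± 39.24% and 27.10% ± 55.12%, and discloses that the SDs were "estimated by dividing the reported post-treatment SD of PVC counts by the baseline mean number of PVCs".

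It then plans on mean reductions that "would be 60% in the intervention group and 35% in the placebo group", "with SDs of 39% and 55%, respectively", and concludes that "with 95% power at a two-sided significance level of 5%, a total of 95 participants per group would be required". A 10% allowance for loss brings this to 106 per group, 212 in all.

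Section 2.14.1 defines the primary outcome for each patient: baseline count minus week-8 count, "then dividing the result by the baseline" count of that same patient. The inclusion criteria (2.5) admit more than 500 PVCs per 24 h, or paired or consecutive PVCs with no minimum count.

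**The concern.** Dividing a count SD by a group-mean baseline gives the SD of the percentage reduction only if every patient has the same baseline. The earlier trial's baselines did not: their SDs were 7,597 and 5,929. The SD of a per-patient ratio also depends on how closely the post-treatment count follows that patient's own baseline, and 2.10 gives no correlation. The mean reductions have the same feature, since 62.44% and 27.10% are reductions of group means rather than means of patients' reductions.

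The SDs are the input on which the number of patients turns. If they do not describe the endpoint, the 95% power does not either, and a null result could not be read against it.

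**Working it through.** **1. Reproducing the plan.**

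- SDs: 5,940/15,138 = 39.24%; 8,009/14,529 = 55.12%.
- Reductions: 1 − 5,686/15,138 = 62.44%; 1 − 10,592/14,529 = 27.10%.
- n per arm = (1.960 + 1.645)² × (39² + 55²)/25² = 94.5, so 95.
- Power at 95 per arm = Φ(25/√((39² + 55²)/95) − 1.960) = Φ(3.614 − 1.960) = 95.1%.
- 95/0.90 = 105.6, so 106 per arm and 212 in total.

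Every figure reproduces. The issue is what the SDs measure.

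**2. SD of the per-patient ratio.** Assume that baseline and post-treatment counts are jointly lognormal with log-scale correlation r. This is an assumption; the protocol gives neither the distribution nor r. For each arm:

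- v_b = ln(1 + CV_b²) and v_p = ln(1 + CV_p²)
- v = v_b + v_p − 2r√(v_b·v_p)
- SD of percentage reduction = 100 × R × √(e^v − 1), where R is the mean of post/baseline.

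CVs from the figures in 2.10:

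- Active: CV_b = 7,597/15,138 = 0.502 and CV_p = 5,940/5,686 = 1.045, so v_b = 0.225 and v_p = 0.738.
- Placebo: CV_b = 5,929/14,529 = 0.408 and CV_p = 8,009/10,592 = 0.756, so v_b = 0.154 and v_p = 0.452.

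R is set to the protocol's planned means: 1 − 0.60 = 0.40 and 1 − 0.35 = 0.65. The SDs and the 25-point difference then belong to the same scenario.

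Example at r = 0: v = 0.962 and 0.606; SDs = 40√(e^0.962 − 1) = 50.9% and 65√(e^0.606 − 1) = 59.3%; SE = √((50.9² + 59.3²)/95) = 8.02; power = Φ(25/8.02 − 1.960) = 88%.

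| r | SD active / placebo | Power, 25 points, 95 per arm |
|---|---|---|
| 0 | 51% / 59% | 88% |
| 0.2 | 44% / 52% | 94% |
| 0.3 | 41% / 49% | 97% |
| 0.5 | 34% / 42% | above 99% |

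At r = 0, 95% power would need 128 per arm. The stated 95% is met at r of about 0.22.

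**3. If the SD is larger in this population.** The earlier trial's patients averaged about 15,000 PVCs per day. Among patients who enter with few, a modest absolute rise is a large negative percentage. The documents give no baseline distribution for this population, so only a generic sensitivity is possible: power = Φ(25/(SD × √(2/95)) − 1.960).

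| Common SD | Power at 95 per arm | n per arm for 95% |
|---|---|---|
| 48% | 95% | 96 |
| 55% | 88% | 126 |
| 60% | 82% | 150 |
| 70% | 69% | 204 |
| 80% | 58% | 267 |

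Power falls below 90% once the common SD exceeds about 53%, and below 80% once it exceeds about 61.5%.

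**The case against.** The strongest defence is that this is a disclosed approximation, not a miscalculation, and that it lands close to the right place. That stands for a population like the earlier trial's: with any moderate correlation between a patient's two counts, power is at or above about 94%, and it is 88% even with none. The protocol also planned on a 25-point difference when the earlier trial's was 62.44 − 27.10 = 35.3 points, which is a real margin. The primary model (2.17) adjusts for center and baseline count, and 2.10 takes no credit for any precision this may recover.

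A reader might go further and infer power of only about 70%, with 200 per arm needed. That figure comes from keeping the earlier trial's mean counts at r = 0. The SDs are then 60% and 78%, but the mean reductions that go with them are 53% and 15%, a 38-point difference. Pairing those SDs with 25 points mixes two scenarios; with their own 38 points, power at 95 per arm is about 97%. The 70% figure is not supported.

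What the defence does not answer is that the closeness depends on a correlation that 2.10 neither states nor justifies, and on a population with much higher baseline counts than the entry criteria require.

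**Conclusion.** The point holds as a misdescribed input. The 39% and 55% are not SDs of the primary endpoint, and the 95% power derived from them is unsupported. In a population like the earlier trial's, power at 95 per arm runs from about 88% with no correlation to above 99% at correlation 0.5, assuming lognormal counts and the planned means. With common SDs of 55% to 80%, it would be about 88% to 58%.

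It would be tempting to conclude that the trial is underpowered, but the documents do not show that. The true SD may be smaller or larger than planned. The low entry threshold is a reason to expect a larger one, but its effect cannot be quantified from the article. The validity of the primary analysis is not affected.

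**What to change.** Keep 212 participants and correct section 2.10:

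- State that 39% and 55% are approximations obtained from 4-week count SDs over group-mean baselines, and are not SDs of the per-patient percentage reduction.
- Replace the single 95% with power for a 25-point difference at 95 evaluable per arm over a stated range of per-patient SDs, for example 48% to 80% (about 95% down to 58%). Alternatively, give a justified per-patient SD, or the correlation assumed.
- Optionally, check the pooled SD of the endpoint on blinded data; this does not reveal the treatment effect.

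The cost is a rewording and a less favourable stated power. No patients are added and the analysis does not change.
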